## **9. Data Collection and Management**

### *9a. Sources of data*

The study will collect data from five sources, as follows:

1. Pre-screening logbook. Aggregate statistics about the number of potentially eligible patients not screened for the study will be calculated from logbooks completed by clinic staff.
2. Screening form. Screening forms will be completed to confirm study eligibility and consent.
3. Case report form. The study assistant and study clinician will use the CRF to record all information gathered directly from the patient, including the questionnaire and four SLATE screens.
4. Medical records. Routinely collected medical record data will be abstracted from medical records maintained by the study site and by central repositories (e.g. laboratory database) in electronic and paper format.
5. Facility-level records. We will use aggregate information from the study sites to estimate the overall proportion of patients presenting at each clinic who could start ART immediately if SLATE were used in routine care and the resources that would be required.

### *9b. Pre-screening logbook*

As explained above, where feasible we will ask clinic registration staff to complete one row of a pre-screening logbook for each patient who is offered referral to the study assistant for screening. The logbook will have only five fields: date of visit, sex, age in years, primary reason for clinic visit (HIV test, CD4 count, pre-ART monitoring, adherence education session, ART initiation), and whether the referral to the study assistant was accepted (yes/no). No identifiers of any kind will be collected in this logbook, which is intended to provide only aggregate information. Data from the logbook will be used to estimate the total volume of patients who could benefit from SLATE if it were adopted as standard care and to compare the characteristics of patients who do enroll in the study with those of the overall patient population at the site.

### *9c. Screening form*

The study assistant will complete a screening form for each patient referred after pre-screening. The screening form will record whether the patient meets each inclusion and exclusion criterion and provides written informed consent. For patients enrolled, the Study ID number and medical record number will be added to the screening form, which will become part of the case report form for study subjects. For patients who screen out, it will record the reason for ineligibility.

For female patients, the results of the pregnancy test conducted after consent will be recorded on the screening form, as pregnancy is an exclusion criterion for the study. No case report form will be opened for patients who have positive pregnancy tests.

### *9d. Case report form*

The case report form will have eight sections. Sections 1, 7, and 8 will be completed for standard group patients. All sections will be completed for intervention group patients.

1. A short, closed-ended questionnaire to be administered by the study assistant after consent. The questionnaire will elicit basic information about:
  - Patient characteristics (age, sex, marital status, household composition, duration living in current location, education)
  - HIV-related information (familiarity with clinic, time of diagnosis, acquaintance with others with HIV or on ART)
  - Activities and employment
  - Costs to patient of making a clinic visit (transport costs, loss of income, etc.)
  - Patient's preferences regarding ART initiation (single visit, multiple visits, intervals between).
2. Symptom report. The symptom report form will record yes/no to the presence of the symptoms listed above and provide a space for the study clinician to describe or comment on symptoms and to state whether the patient is ineligible for immediate ART initiation due to symptoms.
3. Medical history. The medical history form will record answers to the medical history questions and provide a space for the study clinician to describe or comment on these answers and to state whether the patient is ineligible for immediate ART initiation due to medical history.
4. Physical exam. The physical exam form will record findings of the physical exam and provide a space for the study clinician to describe or comment on these findings and to state whether the patient is ineligible for immediate ART initiation due to the outcome of the medical exam.
5. Readiness assessment. The readiness assessment form will record answers to the readiness questions and provide a space for the study clinician to describe or comment on these answers and to state whether the patient is ineligible for immediate ART initiation due to readiness.
6. Blood draw. The blood draw form will confirm that a blood sample was taken and record the identification number or bar code used to identify the sample on the CD4 count laboratory order form.
7. Patient identifiers. The identification form will capture identifying information about the subject, including name, date of birth, clinic ID number, and national identification number. This information will not be entered into the study database but will be used only for matching CRF and medical record data.
8. Completion form. The last page of the CRF will confirm data collection and close the study visit for the patient.

#### *9e. Medical record data*

Once the CRF has been completed, all remaining patient-level data for the study will be collected from routinely maintained medical records. The format of these records will vary by study country and site. Some sites will use electronic medical records, while others will rely on paper-based records and registers or a combination of electronic and paper. We will access all available records for each study

patient, regardless of format or storage location, to try to obtain as complete a study data set as possible. The fields we will aim to capture are listed below.

*To be used to link electronic and paper-based records to study identification number only:*

- Electronic medical record system number
- Clinic file numbers
- National ID number
- Name
- Date of birth
- Sex

*All subjects at clinic visit on date of study enrollment:*

- Date of positive HIV test (if available)
- CD4 count (most recent)
- Date and result of TB symptom screen, if done
- Date, type, and result of TB test(s) (current and previous, if any)
- TB treatment, if offered (date of initiation)
- WHO stage and clinical conditions

*Subjects who are eligible for ART initiation at the study clinic:*

- Reasons for delaying ART initiation, if relevant
- Date ART initiated (first dose of drugs dispensed)
- First-line regimen prescribed

*For all clinic visits for duration of study follow up, from study enrollment to the follow-up endpoints indicated above:*

- Date of visit
- Primary reason for visit (e.g. pre-ART visit, scheduled medical visit, medication pickup, unscheduled medical visit)
- Types of professionals seen (e.g. nurse, doctor, pharmacy assistant, counselor)
- Group and individual sessions attended (e.g. wellness course, adherence education)
- Numbers and types of all lab tests conducted (including CD4 counts, viral loads, CrAg test, blood tests to determine ARV regimen)
- Other procedures (e.g. x-rays) performed
- Medications prescribed and dispensed (ARV and non-ARV, including isoniazid and cotrimoxazole)
- Admissions for inpatient care since previous visit, if recorded
- Details of inpatient care received (facility, number of days, medications, lab tests, etc.) if recorded

*At follow-up endpoints (6 and 12 months after ART initiation or comparable timepoint for those who do not initiate ART):*

- Date and result of most recent viral load test
- Status at clinic (in care / died / transferred to another site / stopped care / lost to follow up, defined as > 1 month late for last medication pickup)
- New or recurring HIV-related conditions
- Date and cause of death if applicable
- Date and result of most recent CD4 count

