In an earlier clinical trial in South Africa (RapIT, H-31880), we demonstrated that same-day treatment initiation, in which all the steps required for ART initiation are performed in sequence during a single clinic visit, significantly increased the proportion of eligible patients started on treatment (RR 1.36, 95% CI 1.24–1.49) and the proportion virally suppressed six months later (RR 1.26, 95% CI 1.05–1.50). The RapIT trial was premised on the notion that standard of care treatment initiation, which in South Africa required 5 or 6 clinic visits over a 1-2 month period, created a burden on patients that deterred many from completing the process. In addition to delaying the start of treatment, each clinic visit entailed transport costs and time, many hours of waiting time in the clinic, and possibly lost wages, child care, and other costs for the patient. The results of the study indicate that accelerating the initiation process does overcome these barriers; in the intervention arm of the study, 75% of study subjects started treatment on the same day as study enrollment, and nearly all the rest within one month. The study demonstrated that it is possible to initiate nearly 100% of eligible patients, and eliminate loss to follow up at this point in the care cascade.

Although RapIT and other studies have shown that the vast majority of patients presenting for HIV care at clinics in Africa can safely start ART on the same day, without delay, there are still patients for whom a delay is necessary. These reasons include:

- Tuberculosis (TB): To minimize the risk of immune reconstitution inflammatory syndrome (IRIS), two weeks of TB treatment is recommended for patients presenting with active TB before ART is started.
- Cryptococcal meningitis (CM): Patients with low CD4 counts should be screened for cryptococcal antigen (CrAg) and given presumptive treatment for CM before ART is started, again to minimize the risk of IRIS.
- Other clinical conditions: HIV patients present with a range of symptoms and conditions that may lead a clinician to decide to delay ART while further investigations or treatment are completed.
- Patient history: Patients who previously defaulted from ART or have a history predicting non-adherence, such as substance abuse, may require additional support before starting ART.

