##### *4b. Secondary objectives*

The secondary objectives of this study are to:

3. Compare the proportion of study-eligible patients who initiate ART within 14 days of study enrollment between HIV-infected patients offered immediate ART initiation under the SLATE algorithm and patients offered standard ART initiation.
4. At sites where viral load data are available, compare the proportion of study-eligible patients who initiate ART and are virally suppressed eight months after having an HIV test or enrolling in HIV care
5. Compare the proportion of study-eligible patients who initiate ART and are alive, in care, and retained on ART by 14 months and 16 months after study enrollment between HIV-infected patients

offered immediate ART initiation under the SLATE algorithm and patients offered standard ART initiation.

6. Estimate the proportion of HIV-positive patients presenting at study clinics and not yet on ART who are eligible or ineligible for immediate initiation using SLATE algorithm criteria.
7. Describe reasons for ineligibility for immediate initiation, among those found ineligible in the intervention arm.
8. Estimate average time interval in days between study enrollment and ART initiation for each study arm.
9. Describe self-reported patient preferences on the speed and timing of ART initiation.
10. Estimate costs to patients of implementing the SLATE algorithm, compared to standard care.
11. Estimate costs to providers of implementing the SLATE algorithm, compared to standard care.

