## **12. Outcomes and Data Analysis**

### *12a. Outcomes*

The primary outcomes for the study are:

1. The proportion of patients initiated on ART within 28 days of study enrollment. While national guidelines recommend ART initiation within two weeks of a patient's first clinic visit or HIV diagnosis, recent studies suggest that 28 days is a more realistic deadline for routine care.

2. The proportion of patients who initiate ART and are alive, in care, and retained on ART eight months after study enrollment. Eight months was selected to allow up to 1 month (28 days) to initiate ART, six months of follow up after treatment initiation, and up to 1 month to return for the six-month routine clinic visit.

These outcomes were proposed in a paper published by the investigators based on the MATI technical consultation described in protocol section 3c.

Secondary outcomes will include:

3. The proportion of patients initiated on ART within 14 days of having an HIV test or enrolling in HIV care.
4. The proportion of patients who initiate ART and are virally suppressed eight months of having an HIV test or enrolling in HIV care between HIV-infected patients offered immediate ART initiation under the SLATE algorithm and patients offered standard ART initiation.
5. The proportions of patients who initiate ART and are alive, in care, and retained on ART 14 and 16 months after having an HIV test or enrolling in HIV care. Fourteen months extends the primary outcome endpoint, which is at 8 months, by an additional six months. Sixteen months allows loss to follow up at 12 months to be defined as three months late for the 12-month visit, which is a common endpoint in the literature (16 = 1 month to initiate ART + 12 months' follow up + 3 months to attend 12-month visit).
6. The proportions of HIV-positive patients presenting at study clinics and not yet on ART who are eligible and ineligible for immediate initiation using SLATE algorithm criteria.
7. Reasons for ineligibility for immediate initiation, among those found ineligible in the intervention arm.
8. Average time to ART initiation (days) for each arm.
9. Patient preferences on the speed and timing of ART initiation.
10. Costs to patients of ART initiation under standard and intervention procedures.
11. Costs to providers of ART initiation under standard and intervention procedures.

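### Outcome 4 is timed from HIV test or enrolment, but the viral load that feeds it is abstracted by time since ART start

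*Protocol*

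**What the plan says.** Section 12a defines outcome 4 as "The proportion of patients who initiate ART and are virally suppressed eight months of having an HIV test or enrolling in HIV care". Objective 4 in section 4b uses the same starting point and limits the comparison to sites "At sites where viral load data are available". The study takes no viral load sample of its own: section 7e rules out study visits after baseline, and section 9e says that "all remaining patient-level data for the study will be collected from routinely maintained medical records".

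The field that supplies the result is in section 9e: "Date and result of most recent viral load test". It stands in a list introduced by "At follow-up endpoints (6 and 12 months after ART initiation or comparable timepoint for those who do not initiate ART". A separate visit-level list in 9e records the numbers and types of laboratory tests, viral loads included, but does not ask for their results.

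For the primary retention outcome, section 12a explains the eight months: "Eight months was selected to allow up to 1 month (28 days) to initiate ART, six months of follow up after treatment initiation", and then "up to 1 month to return for the six-month routine clinic visit".

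Two places bear on how late standard-care patients start. Section 3b describes standard initiation at the time of the earlier South African same-day trial, "which in South Africa required 5 or 6 clinic visits over a 1-2 month period". Section 12a says that guidelines recommend initiation within two weeks and that 28 days is more realistic for routine care.

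**The concern.** The outcome runs from HIV test or enrolment; the field runs from ART start. Staff who follow 9e as written read a same-day starter at about month 6 and a day-60 starter at about month 8, so the arms are read at different times after enrolment. Staff who follow 12a read everyone at month 8, when patients who started later have had less time for a six-month test to be done. Either way, the chance of having a usable result depends on when ART started, and start date is what the intervention is designed to change.

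The HIV-test alternative adds a further looseness. Section 5c admits patients diagnosed at any earlier time, for whom eight months from the test may have little relation to randomization.

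At stake is the trial's only virological outcome. A difference between arms could mix true suppression with whether a test had yet been done.

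**Working it through.** **1. The plan's own build-up.** 1 month to start + 6 months on ART + 1 month to attend = 8 months. It reproduces for starts within 28 days: 28/30.44 + 6 + 1 = 7.92 months.

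**2. When a six-month test falls.** Assumption: a routine viral load is due six months after ART start. Due month = start day/30.44 + 6; add 1 for a visit one month late.

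| ART start (day) | Due (month) | One month late |
|---|---|---|
| 0 | 6.00 | 7.00 |
| 28 | 6.92 | 7.92 |
| 30 | 6.99 | 7.99 |
| 60 | 7.97 | 8.97 |
| 90 | 8.96 | 9.96 |

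Month 8 is missed by starters after about day 60 if they attend on time, and by starters after about day 30 if they attend a month late.

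**3. Test coverage by month 8.** Further assumptions: test due 182 days after start, cut-off day 243, attendance delay exponential with mean m. The slack for a start on day s is 243 − 182 − s = 61 − s, so

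P(tested by day 243) = 1 − exp[−(61 − s)/m].

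With m = 21 days: day 0, 94%; day 28, 79%; day 45, 53%; day 60, 5%.

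For starts spread evenly over days a to b, average coverage = 1 − [m/(b − a)] × {exp[−(61 − b)/m] − exp[−(61 − a)/m]}:

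- Days 7–28: 1 − (21/21) × (0.2078 − 0.0764) = 86.9%.
- Days 7–60: 1 − (21/53) × (0.9535 − 0.0764) = 65.2%.

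Let a share q of the intervention arm start on day 0 (94.5% coverage) and the rest start like the standard arm. The gap between arms is q × (94.5% − standard coverage). For q I use 32% and 67%, the lowest and highest expected screen-in proportions in section 11.

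- Standard starts in days 7–28: 0.32 × 7.66 = 2.4 points to 0.67 × 7.66 = 5.1 points.
- Standard starts over days 7–60: 0.32 × 29.28 = 9.4 points to 0.67 × 29.28 = 19.6 points.

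For mean delays of 14 to 30 days, the ranges are about 1–7 points and 7–22 points respectively. The start distribution matters most, and the protocol does not give it.

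**4. From coverage to suppression.** Coverage turns into an apparent difference in suppression only if untested counts as not suppressed. If true suppression were 65% in both arms (an assumption), the false difference would be 0.65 × gap: about 2 to 3 points in the first case and about 6 to 13 points in the second. If late starting were equal in the two arms, it would be zero.

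**5. Effect of a wider window.** Reading to 11 months (about day 335) gives a slack of 153 − s. With standard starts over days 7–60 and m = 30, coverage is 99.4% for day 0 and 97.9% for the standard arm. The gap is then at most 0.67 × 1.5 = about 1 point.

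**The case against.** Several objections carry weight.

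- The protocol gives no viral load schedule. Testing at six months on ART is inferred from the six-month routine visit in 12a and the endpoints in 9e. This stands, and every figure above depends on it.
- The 1–2 month figure describes standard care in an earlier trial. Section 12a points to two to four weeks, and the eight-month build-up covers starts within 28 days even with a visit one month late. This stands, and is why the lower range deserves as much attention as the higher.
- Late starting is not confined to the standard arm, because intervention patients who screen out start under standard care. The calculation allows for this.
- The screen-in proportions come from a South African between-site calculation, and the calculation has everyone starting by day 60 at the latest. Both limit how far the figures carry over to the pooled analysis.
- A suppression threshold, sampling window and rule for untested patients commonly sit in an SAP, so their absence here is not the point. The clock mismatch is in the protocol itself, though, and an SAP cannot use results that 9e does not have abstracted.
- The visit-level list would already let testing rates be reported by arm. True, but it does not ask for the results.

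A reader might also infer that suppressed results from earlier treatment will inflate outcome 4, since 5c requires only that patients not be on ART now. The documents do not support giving this much weight. Test date and ART-start date are both captured, so such results can be excluded, and prior ART should balance by randomization. What remains is minor: once the single most recent result is excluded, the field holds no replacement.

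**Conclusion.** The protocol contradicts itself on the timing of outcome 4: 4b and 12a count from HIV test or enrolment, 9e counts from ART start, and 9e keeps one result per endpoint with no condition that it follow ART start. If routine tests fall due about six months after ART start, later starters may have no result by month 8, and these could be more numerous in the standard arm. The size is uncertain. At a 21-day mean delay the coverage gap is about 2–5 points or about 9–20 points, depending on whether standard starts end by day 28 or run to day 60.

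A reader might infer an established bias of up to 20 points in favour of the intervention. The documents do not support that. The testing schedule, the start dates and the attendance delays are all assumed; the figures are gaps in testing, not in suppression; and the protocol does not say that untested means not suppressed. Outcome 4 is secondary and limited to sites with viral load data, so the primary outcomes are untouched. The point should still be corrected, because the remedy is cheap.

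**What to change.** Reconcile 4b, 9e and 12a as follows:

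- Count outcome 4 from study enrolment in both arms, dropping the alternatives of HIV test and enrolment in care.
- In 9e, replace the single most recent result with the dates and results of all viral loads from enrolment onward.
- Use the result closest to eight months among samples taken after ART start, within one prespecified window that is identical in both arms and wide enough to include a late six-month test. A window of 5 to 11 months after enrolment is one example.
- State how patients without a result in the window count.
- Report test coverage by arm beside the outcome.

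The cost is one abstraction field and one definition. Record review already runs to 14 months (section 8) or 16 months (section 5c), so no extra follow-up is needed. The downside is small: some results will be read after month 8, and the outcome wording should say so.

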#### *9f. Study identification numbers and linking of records*

Upon consenting to participate in the study, each subject will be assigned a random study identification number. This will be a five-digit number in which the first digit indicates the country and the remaining four digits will be a sequential number that does not provide any identifying information.

A password-protected, encrypted linking file will be created in REDCap to link study identification numbers to subjects' names, dates of birth, national identity numbers, and clinic file numbers. These fields are needed to ensure that study ID numbers can be correctly matched to the identification numbers used in the sites medical records. When a subject has been matched to a clinic record, the clinic record number will also be added to the linking file. The linking file will be a separate document from any other study files. Access to the linking file will be limited to the study team, and the file will be stored in a secure location separate from the study database.

